### Blinding

It is not possible for the participants or interventionists to be blinded to the intervention conditions, as individuals will be aware of the program information delivered. Participants will be advised that the study involves the same resilience program, with one group receiving a new session module. A research officer will conduct the measurement sessions, and may become aware of a participant's group allocation during their interaction with participants. The principal investigator (NB) will be responsible for data analyses.

### Compliance and Loss to Follow-up

Except for those who explicitly request no further involvement in the study, all participants will be asked to complete the baseline, post-intervention and follow-up assessment. Attendance at intervention sessions will be recorded, and individuals who miss two sequential sessions (unplanned) will be contacted by phone and encouraged to return. Data will be analyzed on an intention to treat basis.

### Intervention

#### Group 1: READY resilience program

The *READY *program targets five key psychosocial protective factors of (a) positive emotions, (b) cognitive flexibility, (c) life meaning, (d) social support, and (e) active coping strategies that were identified from empirical literature [5]. The intervention approach is based on Acceptance and Commitment Therapy (ACT) [29]. ACT is an empirically based third generation Cognitive Behavioral Therapy that uses acceptance and mindfulness strategies, and commitment and behavior change strategies to produce psychological flexibility and resilience through six core processes: acceptance, cognitive defusion (changing our relationship with thoughts), being present (mindfulness), self-as-context, values and committed action [29]. Reviews of ACT randomized control trials show an overall advantage of ACT compared with control conditions [29-31].

An outline of the *READY *program sessions is presented in Table 1. Each session includes psychoeducation on the protective factor(s) targeted, group discussion, individual reflection, experiential exercises and opportunities to learn practical strategies. Home assignments build on information presented in the sessions and include reflection, self-monitoring and skills practice. Participants receive a detailed workbook that includes program notes (highlighting key themes), sections for critical reflection, learning activities to complete, and inspirational quotations. The learning and reflection activities comprise the *READY *personal plan, which is an individualized resource for participants to apply the generalized information to their specific context and personal style.

**Table 1 T1:** Overview of *READY *Resilience Training Sessions

Session Topic	Protective Factor Targeted
Introduction and Program Overview *READY *resilience model, protective factors, warning signs of low resilience.	
Activity Promotion (group 2 only) Activity benefits, national activity guidelines, step counting & pedometers, identifying preferences, goal setting, barriers & problem solving.	Physical activity
Mindfulness Mindfulness vs mindlessness, mindfulness strategies.	Cognitive flexibility Positive emotions
Defusion 1 Thought fusion, identifying unhelpful thoughts, defusion strategies.	Cognitive flexibility
Defusion 2 Observer self, defusion strategies.	Cognitive flexibility
Acceptance About emotions, responding to emotions, about acceptance, acceptance strategies.	Positive emotions
Mid Program Review Resilient and non resilient characteristics, activating and trouble shooting coping strategies.	Active coping
Life Values and Meaningful Action About values, value identification, meaningful action.	Life meaning
Social Connectedness Types of support, support responses, active and reflective listening, barriers to social connectedness.	Social support
Relaxation and Pleasant Activities Active relaxation exercises, progressive muscle relaxation exercises, pleasurable activities.	Positive emotions
Review and Planning for the Future Resilient and non resilient characteristics, activating and trouble shooting coping strategies.	Active coping

Note. Although different themes are identified for each session, the content in each session is referred to and followed up in subsequent sessions, so as to integrate the material across sessions.

The program will be implemented as 10 × 2.5 hour sessions over 13 weeks (one school term and two weeks of school holidays). Sessions will be in a group format with 10-20 participants per group, and will be led by an experienced psychologist. A detailed trainer's manual has been prepared including learning objectives, outlines, learning activities, handouts and audiovisual materials for each session. Interventionists will be trained by the program authors (NB and KP).

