**Methods/Design:**

In a cluster randomized trial, 95 participants will be allocated to either a waitlist or one of two intervention conditions. Both intervention conditions will receive a 10 × 2.5 hour group resilience training program (*READY*) over 13 weeks. The program targets five protective factors identified from empirical evidence and analyzed as mediating variables: positive emotions, cognitive flexibility, social support, life meaning, and active coping. Resilience enhancement strategies reflect the six core Acceptance and Commitment Therapy processes (values, mindfulness, defusion, acceptance, self-as-context, committed action) and Cognitive Behavior Therapy strategies such as relaxation training and social support building skills. Sessions include psychoeducation, discussions, experiential exercises, and home assignments. One intervention condition will include an additional session and ongoing content promoting physical activity. Measurement will occur at baseline, two weeks post intervention, and at eight weeks follow-up, and will include questionnaires, pedometer step logs, and physical and hematological measures. Primary outcome measures will include self-reported indicators of psychosocial well-being and depression. Secondary outcome measures will include self-reported indicators of stress, anxiety and physical activity, and objective indicators of CHD risk (blood glucose, cholesterol [mmol·L^-1^], triglycerides, blood pressure). Process measures of attendance, engagement and fidelity will also be conducted. Linear analyses will be used to examine group differences in the outcome measures, and the product of coefficients method will be used to examine mediated effects.

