### Sample Size

The sample size is based on detecting a difference in personal well being as measured by Ryff's Scales of Psychological Well-Being [27]. Previous research showed that differences of 3.0 points (SD 4.0) can be detected post intervention [28]. To achieve a similar difference, using a two tailed test with alpha level 0.05 and power of 80%, we will require 28 participants in each of the three groups. Allowing for attrition, we will aim to recruit 30-35 participants per condition.

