### Analyses

Data will be analyzed on an intention-to-treat basis, using random effects mixed modeling to examine group differences in the outcome measures among baseline, post-intervention and follow-up. Linear analyses will be used to examine the potential mediation of the five identified protective factors (see Figure 2). We will calculate the (a) direct effect of the program on the outcome measures (τ); (b) effect of the intervention on each of the mediating variables, adjusted for baseline values (α); (c) the effect of the residual change score (post intervention score adjusted for the baseline score) of the proposed mediating variables on the outcome measures, after adjustment for the intervention (β); and then examine whether there is attenuation or change in significance in the relationship between the intervention and the outcome measures, after adjustment for the change in the mediating variables (τ'). The product of the α and β coefficients will be used to provide an estimate of the magnitude of the mediation effect in the units of the outcome variable, and the 95% confidence intervals of the point estimates of the mediated effects will be examined to test for mediation [41].

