There are some methodological issues to consider with this study. Recruitment of staff from a regional district of a government department may result in a study sample that is not representative of the general population. As participants will be recruited from within one organization, there may be a risk of contamination between intervention conditions if they communicate with each other. However the clustering of individuals by occupational group and geographical location may reduce this risk. Participants receiving the physical activity promotion will receive one more intervention session than those who receive only the psychosocial resilience training. It is unlikely however, that the additional two and a half hour session, in the context of the 25 hour program, will by itself provide marked additional benefits. To minimize potential trainer effects, interventionists will be involved in both group conditions (i.e. resilience training AND resilience training + physical activity promotion).

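### The 80% power at 28 per arm assumes independent individuals, although both active arms are taught in groups and the wait list is not; no term for training group is named, so the 5% error rate is not assured

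*Protocol article*

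**What the plan says.** Protocol article, Sample Size: the calculation starts from earlier research in which "differences of 3.0 points (SD 4.0) can be detected post intervention" and continues: "using a two tailed test with alpha level 0.05 and power of 80%, we will require 28 participants in each of the three groups". The only allowance on top is for dropout: "Allowing for attrition, we will aim to recruit 30-35 participants per condition". The abstract gives the total: "95 participants will be allocated to either a waitlist or one of two intervention conditions".

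Intervention, Group 1: "Sessions will be in a group format with 10-20 participants per group, and will be led by an experienced psychologist". Group 2 receives the same training plus one session and continuing physical activity content. Under Wait list Condition, those participants are seen only for measurement.

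Participants and Randomization: the randomised units are cells of occupation (three categories) by location (two), so at most six. The article does not say how training groups are formed from these cells.

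Analyses: the model is described as "using random effects mixed modeling to examine group differences in the outcome measures among baseline, post-intervention and follow-up". No random effect is named, whether for participant, randomised cluster or training group.

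Discussion: "To minimize potential trainer effects, interventionists will be involved in both group conditions".

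**The concern.** People who share ten sessions, the group discussions and one psychologist tend to end up with more similar outcomes than people who do not. This correlation arises from the treatment, after allocation, and only in the two active arms. It is a separate source from the occupation-by-location cells that are randomised. With 30 to 35 people per condition and 10 to 20 per group, each active arm has only two or three training groups.

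If the correlation is positive, the active-arm means are less precise than the sample size assumes. Group 2 versus Group 1, the added-value question in the stated aim, suffers most because both sides are grouped. Using the same trainers in both active arms limits confounding of trainer with arm. It does not remove correlation within groups and does not bear on active versus wait list.

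**Working it through.** **Inputs.** Difference 3.0, SD 4.0, two-sided alpha 0.05, power 80%, n = 28 per arm (Sample Size); group size m between 10 and 20 (Intervention); wait list ungrouped (Wait list Condition). The training-group ICC is not given. I assume 0.01, 0.05 and 0.10, with the total SD held at 4.0.

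**1. The plan's own figure.** n = 2 × (1.96 + 0.8416)² × (4.0/3.0)² = 27.9, so 28, with power 80.1%. The stated number is reproduced exactly with no design effect.

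**2. Power allowing for training groups (normal approximation).** Design effect in an active arm: DE = 1 + (m − 1) × ICC.
- Active versus wait list: SE = 4.0 × √((DE + 1)/n).
- Group 2 versus Group 1: SE = 4.0 × √(2 × DE/n).
- Power = Φ(3.0/SE − 1.96).

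Example with m = 14, ICC 0.05: DE = 1 + 13 × 0.05 = 1.65. Against the wait list, SE = 4.0 × √(2.65/28) = 1.231 and power = Φ(2.438 − 1.96) = 68%. Between active arms, SE = 4.0 × √(3.30/28) = 1.373 and power = Φ(2.185 − 1.96) = 59%.

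| ICC (assumed) | DE, m = 14 | Power vs wait list | Power, Group 2 vs Group 1 |
|---|---|---|---|
| 0 | 1.00 | 80% | 80% |
| 0.01 | 1.13 | 78% | 75% |
| 0.05 | 1.65 | 68% | 59% |
| 0.10 | 2.30 | 59% | 46% |

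**3. Number needed for 80%.** (4.0 × 2.8016/3.0)² = 13.95, multiplied by (1 + DE) against the wait list and by 2 × DE between active arms. For m from 10 to 20:
- ICC 0.05: 35 to 42 per arm against the wait list, 41 to 55 between active arms.
- ICC 0.01: 30 to 31 and 31 to 34.

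With 35 analysed per arm, ICC 0.05 and m from 10 to 20, power is 81% down to 73% against the wait list and 74% down to 61% between active arms.

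**4. Few degrees of freedom.** With two groups per arm in each comparison and a test on 2 degrees of freedom, the critical value is 4.30 instead of 1.96. At n = 28 and ICC 0.05, power is then about 29% against the wait list and 25% between active arms. Most of this drop comes from the degrees of freedom: at ICC 0 the same test has 35%.

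**5. Error rate.** These are simulated two-sample t-tests that ignore all grouping, 40,000 runs, 2 × 14 per active arm, at ICC 0.01, 0.05 and 0.10:
- Against an ungrouped wait list: about 6%, 9% and 13%.
- Between active arms: about 7%, 13% and 20%.

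A t-test on cluster means (two clusters of 14 per arm, each training group equal to a cluster, training correlation in the active arms only) gives about 5.0% to 5.5% against the wait list and about 5% between active arms.

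**The case against.** The analysis section does not say that participants are treated as independent. It specifies a random effects model without naming the random terms, and a journal article may leave that list to a fuller plan. A reader might infer that the 5% error rate fails even if the randomised clusters are modelled. The documents do not support that. The inflated rates in step 5 come from tests with no clustering term at all. A cluster-level analysis keeps close to 5% when each training group is a cluster, and also when several training groups are nested in one cluster. Only groups that cut across or merge clusters would escape a cluster term, and nothing says this happens. Coincidence is plausible: 95/6 is about 16 people per cell, inside the 10 to 20 range, and about two cells per condition matches two or three training groups.

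The ICC is also assumed. At 0.01 the loss is small, and 30 to 31 per arm would suffice against the wait list, within the recruitment target if nobody drops out. The trainer's manual, trainer training and video fidelity ratings may hold between-group differences down.

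All of this stands as a limit on the error-rate claim and on the size of the loss. It does not rescue the power statement, which is explicit, reproduces only under independence, and adds people only for attrition.

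**Conclusion.** The point holds for power. The stated 80% at 28 per arm is true only for independent individuals and is not delivered for any positive training-group ICC. The loss is slight at ICC 0.01 and material at 0.05 or more, and larger for Group 2 versus Group 1 than against the wait list. The normal-approximation figures are upper limits within the plan's own calculation (SD 4.0, two groups of 14), because two or three groups per arm leave few degrees of freedom.

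For the error rate the conclusion is weaker: 5% is not assured, because no term for grouping is named and the link between training groups and randomised clusters is not stated. It is not shown to be violated. All sizes rest on the assumed ICC range.

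**What to change.** 1. In Sample Size, replace the single 80% figure with a power range over a stated ICC range, computed with the same degrees of freedom as the planned test, and say that 80% applies only to independent individuals. Normal-approximation values such as 68% and 59% should not be printed beside a test that uses small-sample degrees of freedom.
2. In Analyses, state that training groups are formed within randomised clusters, and fit a random effect for cluster with small-sample degrees of freedom. If groups will cross or merge clusters, add a random effect for training group in the two active arms at the post-intervention and follow-up visits.

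I would not add an interventionist factor or further group terms in the mediation models: two or three groups per arm cannot support them.

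The cost is wording, a record of who trained in which group, wider intervals and a less favourable stated power. No participants or procedures are added.

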#### Group 2: READY resilience program plus physical activity promotion

Participants will receive the resilience training described for Group 1, as well as an additional session and ongoing content promoting physical activity. The session will include psycho-education on physical activity and resilience; a review of national physical activity guidelines; discussion of step counting and pedometer use; consideration of preferred types of physical activity; goal setting; strategies to redress barriers to physical activity, and planning and problem solving for relapsing participation. Walking, both purposive and incidental, will be specifically promoted as a physical activity option requiring no resources. Participants will be given a pedometer (step counter) and logbook, and will receive instruction and rehearsal on how to wear and use the pedometer for self-monitoring. Subsequent sessions will include a check on progress with physical activity goals, and discussion on how to apply resilience strategies to facilitate physical activity participation e.g., obtaining social support, identifying associated values, using cognitive strategies to redress negative thoughts.

### Wait list Condition

Participants allocated to this condition will receive no contact during the study period, apart from measurement sessions. Participants will be offered the most efficacious intervention condition after the trial.

### Measures

Participants will attend group assessment sessions at a local venue. Data will be collected at baseline, two weeks after the intervention period, and again after a further eight weeks. Self-report data will include questionnaire information on psychosocial functioning, physical health, physical activity participation, sociodemographic characteristics (measured only at baseline), and program feedback (measured at post-intervention and follow-up). Participants will be asked to provide pedometer step counts for seven consecutive days. Physical data will include objectively measured height and weight, waist circumference and systolic and diastolic blood pressure. Haematological data will require a finger prick capillary blood sample to assess triglycerides, cholesterol and glucose. Process measures will include participant attendance and self-rated involvement with home assignments, as well as assessment of the fidelity of the intervention delivery.

#### Primary outcome measures

A self-administered battery of psychological questionnaires will be used to derive outcome measures. Unless stated, all items use the previous three months as the referent period.

1. Ryff's Scales of Psychological Well-Being assesses six areas: autonomy, environmental mastery, personal growth, positive relations with others, purpose in life, and self-acceptance [27]. Each sub-scale consists of nine items and responses are scored on a six point Likert scale (1 *strongly disagree *to 6 *strongly agree*). This measure is widely used, has well established reliability and validity [6], and has previously been shown to be sensitive to detecting treatment effects [28].

2. The Center for Epidemiological Studies Depression Scale (CES-D) has 20 items and assesses self reported symptoms associated with depression [32], including affective, somatic, cognitive, motivational and interpersonal dimensions. Responses are scored on a four point Likert scale (0 *rarely or none of the time [less than one day/week] *to 3 *most or all of the time [5-7 days/week]*). This is one of the most commonly used self report questionnaires on depression for the general (vs clinical) population, and has established reliability and validity [32].

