#### Secondary outcome measures

The following measures will also be used. Sequentially, resting blood pressure will take place prior to the finger-prick blood sample and then the physical measures. Questionnaires will be done during the assessment session.

1. The Short Version of the Depression Anxiety Stress Scale (DASS-21) has 21 items and consists of three subscales: depression, anxiety and stress [33]. Items ask respondents to indicate the frequency of intra-personal experiences, such as finding it hard to wind down, on a four point Likert scale (0 *not at all *to 3 *most of the time*). Each subscale has demonstrated high internal consistency and yielded meaningful discriminations in a variety of settings in both Australian clinical and community samples [33].

2. Physical activity participation will be assessed via self-report using items adapted from the Active Australia surveys to assess the total time spent during the last week (i) walking briskly for recreation or exercise (adapted to exclude walking to get to and from place to place), (ii) doing moderate physical activity, like social tennis, swimming, golf, (iii) doing vigorous physical activity like aerobics, cycling, running [34]. Two additional items will be used to assess total time spent walking for transport and cycling for transport. Total time spent in recreational physical activity will be calculated by summing time spent in minutes across the three categories, with time in vigorous activity weighted by a factor of two to reflect greater intensity i.e., Σ[minutes walking + minutes moderate activity + (minutes vigorous activity × 2)]. Total time spent in transport activity will be calculated by summing time spent in minutes of walking and cycling for transport. Physical activity will also be assessed using pedometer step counts. Participants will be asked to wear a pedometer for seven consecutive days and record the total number of steps taken each day; this data will be used to derive average daily step counts.

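### With a three-month recall period, the assessment two weeks after a 13-week program asks mostly about the training weeks, which dilutes an effect that builds up and blurs the comparison with follow-up

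*Protocol article*

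**What the plan says.** The protocol article, under Primary outcome measures, introduces the self-administered psychological questionnaires with the rule "Unless stated, all items use the previous three months as the referent period". The two primary scales follow:

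- **Ryff's scales.** "Each sub-scale consists of nine items and responses are scored on a six point Likert scale", running from strong disagreement to strong agreement. No recall period is given.
- **CES-D.** Twenty items scored by frequency, with the lowest category "rarely or none of the time [less than one day/week" and the highest five to seven days a week. No recall period is given.

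The default of three months therefore governs both. Where another period is meant, the article says so: the physical activity items under Secondary outcome measures are worded "to assess the total time spent during the last week".

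On timing, the Group 1 intervention section sets the program as "sessions over 13 weeks (one school term and two weeks of school holidays". The Measures section states: "Data will be collected at baseline, two weeks after the intervention period, and again after a further eight weeks". The Analyses section compares the groups across baseline, post-intervention and follow-up in a mixed model. Sample Size bases the trial on Ryff: "Previous research showed that differences of 3.0 points (SD 4.0) can be detected post intervention".

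**The concern.** A respondent who follows the instruction at the post-intervention assessment reports on a period that began about two weeks into the program. Table 1 delivers the protective factors one after another, and values, social connectedness and relaxation come after the mid-program review. The answer therefore averages in weeks before much of the content had been taught. If the benefit grows as sessions accumulate, the difference from the wait list at this assessment is smaller than the difference in participants' state at that time.

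The pattern over time is affected too. The follow-up window lies mostly after the program and the post window mostly within it, so a rise from post to follow-up could come from the recall period alone.

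The CES-D has a further difficulty. Its answer categories describe a typical week. Over three months in which symptoms may change, no single number of days per week need apply.

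**Working it through.** **Inputs.** Program 13 weeks (Group 1 intervention section). Assessments 2 weeks after its end and 8 weeks later (Measures). Recall three months, taken as 13 weeks (Primary outcome measures). Planning difference 3.0, SD 4.0, two-sided alpha 0.05, power 80%, 28 per group (Sample Size).

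**1. The plan's own figure.** Normal approximation: n = 2 × (1.96 + 0.84)² × (4.0/3.0)², which rounds up to 28 per group, so the stated figure reproduces. Power at 28 per group is 80.1% by the normal approximation and 78.7% by the t-test. Neither allows for clustering.

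**2. What each window covers,** in weeks elapsed since program start:

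| Assessment | Week | Window | Training weeks recalled | Weeks after training |
|---|---|---|---|---|
| Post-intervention | 13 + 2 = 15 | 2 to 15 | 11 of 13 (85%) | 2 of 13 (15%) |
| Follow-up | 15 + 8 = 23 | 10 to 23 | 3 of 13 (23%) | 10 of 13 (77%) |

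The windows share weeks 10 to 15, which is 5 weeks. If three months is read as 12 weeks, the training shares are 10/12 = 83% and 2/12 = 17%.

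**3. Share of the full effect retained.** This step needs two assumptions that the article does not supply: a curve for how the effect builds up, and equal weight for every recalled week. The retained share is the mean of the curve over the window.

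Linear build-up to the full effect at week 13, then held:

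- Post: [(13² − 2²)/26 + 2]/13 = (6.35 + 2)/13 = 0.642
- Follow-up: [(13² − 10²)/26 + 10]/13 = (2.65 + 10)/13 = 0.973

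Other curves, at the post assessment:

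- Full effect at mid-program (week 6.5), linear before that: [(6.5² − 2²)/13 + 8.5]/13 = 0.88
- Exponential rise with a 4-week half-time, full at week 13: 0.80
- Effect only once the program ends: 2/13 = 0.15 (follow-up 10/13 = 0.77)
- Full effect from the first week: 1.00, no dilution

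**4. Illustrative power, 28 per group, SD 4.0, each assessment taken alone:**

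| Curve | Post: difference | Post: power (normal / t) | Follow-up: difference | Follow-up: power (normal / t) |
|---|---|---|---|---|
| Linear | 1.93 | 43.7% / 42.5% | 2.92 | 78.0% / 76.5% |
| 4-week half-time | 2.40 | 61.3% / 59.8% | 2.97 | 79.5% / 78.0% |
| Immediate | 3.00 | 80.1% / 78.7% | 3.00 | 80.1% / 78.7% |

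Under the linear curve, 80% power at the post assessment would take 68 per group.

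**5. The time pattern.** With linear build-up and full maintenance, the true effect is the same at weeks 15 and 23, but the windows show 64% and then 97%. Now suppose the effect declines linearly from its week-13 peak to half by week 23. The true values are 0.90 at week 15 and 0.50 at week 23. The window averages are:

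- Post: (6.35 + 1.90)/13 = 0.63
- Follow-up: (2.65 + 7.50)/13 = 0.78

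A real decline would then be recorded as a rise.

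**The case against.** **The power figure.** A reader might infer that the trial has only about 42% power. The documents do not support that.

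- The 3.0-point difference is for Ryff, whose items are agree/disagree statements. Respondents may well answer about how they are now, and equal averaging over 13 weeks fits these items least.
- The recall period behind the 3.0 points is not given. If the earlier research used a similar window, the figure already includes the dilution.
- The SD is held at 4.0 for every recall length, without evidence either way.
- The mixed model uses both later assessments, and under the same linear curve follow-up loses almost nothing.

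All of this stands, and it limits the power figure to an illustration for the post assessment.

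**Maintenance.** A reader might also infer that maintenance cannot be judged at all. That goes too far: 8 of the 13 follow-up weeks are not shared with the post window, and 10 of 13 lie after the program. The comparison is blurred and can mislead, but it is not impossible.

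**Mediation.** It is tempting to add that the three-month rule makes the mediator and outcome windows coincide. They would coincide under any common recall period, including a short one, so this is not a consequence of the rule.

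**Severity.** The same instruction applies in all three arms, and the dilution at the post assessment runs toward the null. The randomized comparison is intact, and the dilution does not produce a false claim of benefit there. That also stands.

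What remains is that the article states the rule, that the calendar follows from its own figures, and that it neither acknowledges nor justifies the overlap.

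**Conclusion.** The point holds and should be fixed, though it does not invalidate the trial. The protocol's own dates establish that 85% of the recalled period at the post-intervention assessment (83% if three months is 12 weeks) is training time.

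The direction of the bias, toward the null at that assessment, follows for any effect that builds up over the sessions, provided respondents recall as instructed. Its size is not established. The retained share ranges from 15% to 100%, with 64% under linear build-up and 80% under the 4-week half-time, and every value rests on an assumed curve and equal weighting of weeks.

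The firmest case is the CES-D, where a days-per-week scale is paired with a three-month period. For Ryff the case is weaker. The distortion from post to follow-up matters as much as the lost power, since it can suggest a late gain or hide a decline.

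**What to change.** Before baseline data are collected:

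- Replace the three-month default for the CES-D and the other frequency-type psychological scales with a period that lies within the two weeks after the program: the past week, at most the past two weeks. One week also agrees with the CES-D anchors.
- State whether Ryff is answered as current state or over that same short period.
- Use identical wording at baseline, post-intervention and follow-up.

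The cost is a line of questionnaire instructions. There are two downsides. Scores become less comparable with any earlier use of the three-month wording. A short window is also more sensitive to the school calendar, since participants are education staff and the program spans a term and holiday weeks.

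If baseline has already been collected under the three-month instruction, changing the wording later would break comparability with it. The report should then say that the post-intervention scores mainly cover the training period, and read the change from post to follow-up with that in mind.
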